## BACKGROUND

Malnutrition is highly prevalent in the elderly population, ranging from 5-10% in community-dwelling individuals to more than 50% in hospitalized patients and those in rehabilitation and long-term care. Our prior study (funded by the Helen McCall Hutchison Foundation) of frail elderly patients enrolled in the MUHC-Geriatric Day Hospital (GDH) rehabilitation program revealed that 6% of new attendees were frankly malnourished, an additional 13% were moderately malnourished and overall, 53% were at risk of malnutrition. Malnutrition was associated with lesser muscle and fat mass, and handgrip strength, a measure of muscle strength. Scores of malnutrition (from the Mini-Nutritional Assessment, MNA) correlated with gait speed, a strong indicator of physical performance, mobility and even morbidity. These findings justify testing a nutritional intervention aiming at improving nutritional status and physical performance of the GDH participants.

The comprehensive GDH program includes individualized physiotherapy, occupational health, nursing and medical care for rehabilitation of patients with loss of autonomy after hospitalization, falls, or rapid decline in their ability to perform activities of daily living. Unfortunately, no dietetic counseling is offered as part of the program. Therefore, for an eventual implementation of the program, our proposed intervention has to be pragmatic, feasible and targeted towards the main nutrients known to affect physical functioning, namely protein and vitamin D and possibly omega-3 fatty acids.

*Dietary Protein Recommendations and Supplements.* The official Recommended Daily Allowance (RDA) of protein for the elderly is currently actively debated and the suggestion to revise it upward is endorsed by many experts. All acknowledge that the RDA should not merely cover the minimal protein needs to avoid deficiency but rather, the amount to minimize lean tissue loss, sustain optimal health and maintain an active living. In the Health, Aging and Body Composition study including 2066 men and women of 70-79 years, the loss of total lean and appendicular muscle mass was less in the highest quintile of energy-adjusted protein intake of 1.2 g/kg/d than in the lowest quintile of 0.8 g/kg/d. Likewise, analysis of a subset of the Women's Health Initiative study (n=24,417 women, 65-79 years) determined a 32% lower risk of developing frailty over 3 years associated with a 20% increase in calibrated protein intake (as % of energy). From these and other studies, a protein intake of at least 1.2 g/kg/day should be advised.

The positive impact of protein supplementation on increasing gains in muscle mass and strength during prolonged resistance-type exercise is well demonstrated in young and older adults. However, the role of protein supplement alone, in persons who cannot or do not want to engage in such exercise is more mitigated and may largely depend on protein quality, dose and the timing of ingestion. Dietary protein contain non-essential and essential amino acids (AA), the latter recognized to be responsible for stimulating muscle protein synthesis and the post-prandial anabolic response. Leucine is the most potent amino acid capable of stimulating protein synthesis through signaling to the intracellular nutrient-sensing mTORC1 resulting in increased mRNA translation and protein elongation. We and others have proposed that a significant increase of circulating leucine is necessary to illicit anabolic effects in

muscle, the so-called anabolic threshold, which is elevated in older and particularly frail persons due to associated conditions such as inactivity, insulin resistance and inflammation.

Increasing protein intake from dietary sources such as meat, fish, dairy and legumes, in frail elderly persons is a challenge for the majority who have decreased appetite, and for many with mastication and digestibility difficulties, and budget limitations. Because large intakes of protein increase satiety and may induce a compensatory decrease in voluntary food intake, it is important to propose supplements of high-quality protein with fewer calories. Whey protein is naturally rich in essential AA, particularly leucine. It is palatable, easy to digest and dissolvable such that it may be provided as a small volume drink, which should not displace usual food intake. Whey protein supplements provided as 2 doses of 20 g per day were tested in mobility-limited elderly with resistance exercise training during 6 months. Significant improvement in muscle mass and strength, and stair-climbing performance were reported due to exercise but only trends for additional benefits of the whey protein supplement were observed. The dose of 20 g per meal occasion may not have been sufficient to reach the anabolic threshold and, supplements were consumed after breakfast and supper. Our last year study, funded by the Helen McCall Hutchison foundation, revealed that a leucine supplement ingested before meals as opposed to within meals generated greater circulating leucine concentrations (both peak and area under the curve). Thus, timing of supplement ingestion should also be considered when designing an intervention to promote muscle protein anabolism.

A recent randomized placebo-controlled trial tested a whey protein supplement of two doses of 20 g enriched with 3 g leucine and 800 IU vitamin D, in sarcopenic, independently living older adults with mobility limitations. Supplements were ingested before breakfast and lunch during 13 weeks. The intervention resulted in more gain in muscle mass and improved chair-stand test, an indicator of muscle strength and power, compared to placebo. No difference in handgrip strength and global score for physical performance were seen. Authors argued that the dose of whey protein may not have been sufficient to improve all aspects of physical performance.

*Vitamin D and muscle health.* Vitamin D deficiency is highly prevalent in older adults. Investigations on the role of vitamin D and physical performance have yielded mixed results. Many studies, but not all, have reported positive associations between serum vitamin D levels and physical performance. The majority of supplementation studies showed positive effects on balance, gait speed and muscle strength, but again, some did not. From a meta-analysis of RCTs, high-dose vitamin D supplements (700-1000 IU), raising serum levels  $\geq 60$  nmol/L, reduced the incidence of falls by 23%, but the low-dose supplements had no effect on falls. It appears that normalizing serum vitamin D levels to sufficiency (50-80 nmol/L) in deficient individuals is desirable to optimize physical performance and high-dose supplements may provide further gains, perhaps additional to those resulting from whey protein and leucine supplement.

*Omega-3 fatty acids.* Long-chain omega-3 fatty acids (n-3 FAs) are essential in the diet and play important roles in organ development and function, including the brain and the heart. Notably, the marine-derived eicosapentaenoic acid (EPA) and docosahexaenoic acid (DHA) have well-known immune-modulating and anti-inflammatory properties and reduce the risk of coronary heart disease and stroke  and overall mortality in older adults . Interestingly, recent studies have also revealed a role of n-3 FAs in bone  and muscle health and function . Supplementation studies in humans have shown that n-3 FAs increased the postprandial stimulation of muscle protein synthesis and resulted in increased muscle mass and strength after 6 month-supplementation, in older adults , and enabled the maintenance of muscle mass of lung cancer patients during chemotherapy . In an Icelandic population-based study, higher plasma phospholipid polyunsaturated FAs were cross-sectionally associated with greater muscle size and leg strength, but not with changes over 5 years . However, increased intake of total n-3 FAs and DHA were associated with lower risk of mobility disability in older women . As well, in the InChianti prospective study, baseline plasma n-3 FA levels were inversely related with the risk of developing impaired physical performance but did not affect gait speed . As with vitamin D, doses may be important. Indeed, 6 month-supplementation of 2 g DHA /day resulted in improvement in walking speed compared to placebo, in postmenopausal women .

Based on the above knowledge, we are aiming to provide a combined supplement consisting of whey protein isolate supplement given in 2 daily doses added with 3 g of leucine, before breakfast and before bedtime. Protein doses of 20 g, 25 g or 30 g of powder will be given according to body weight category. In addition, a supplement of 1.9 g of fish oil (long-chain omega-3 fatty acids EPA and DHA) containing 1500 IU vitamin D will be ingested once daily. Dosages are based on data showing elevating plasma phospholipids EPA + DHA to  $\geq 4\%$  of total FAs and 25(OH)D levels of  $\geq 80$  nmol/L, while being safe.

#### **RATIONALE**

Given the high prevalence of malnutrition of the GDH participants and its impact on poor physical performance, providing a nutritional supplement to increase protein, leucine, vitamin D and omega-3 FA intake should complement and optimize the rehabilitation interventions in improving muscle mass, strength and physical performance.

#### **OBJECTIVES**

Implementing the proposed nutritional supplement in the routine care of GDH participants will:

1. test the feasibility, acceptance and compliance to the supplement and its safety
2. provide pilot data to test the superiority of the supplement versus an isocaloric placebo on measures of muscle mass, strength, physical performance, and mobility.

## METHODS

**Participants.** All newly admitted patients, men and women, referred to the GDH program (of the MGH) who meet eligibility criteria will be invited to participate. Participants must be able to understand study requirements (Mini Mental State Exam, MMSE >22/30) and to read and speak English or French. Participants with the following criteria: BMI >35 kg/m^2, presence of kidney (GFR <30 mL/min/SA), liver or heart failure, stroke in the last 6 months (unless totally recovered), Parkinson's disease, severe neurologic conditions, active malignancies, acute inflammation (CRP >10 mg/L), known diagnosis of hyperparathyroidism, recent acute weight loss (>10% in 3 months, unless stabilized), allergy to milk and/or fish, long-term use of corticosteroids or anti-neoplastic medication, will be excluded from the study. All subjects taking vitamin D supplements  $\geq$  800 IU/d will be asked to reduce their dose to 400 IU/d. If vitamin D supplements were prescribed, the subjects' physician will be informed to change the current prescription to 400 IU/d for the study duration. As for subjects taking any type of omega-3 supplements, they will be asked to cease it for the study duration. All eligible subjects will be approached by the study coordinator and will be provided with an information brochure. Subjects interested in participating will be invited to review study procedures and sign the consent form.

**Study design.** This is a randomized, placebo-controlled, double-blinded pilot trial of two parallel arms. Participants will be randomly assigned to one of two groups: experimental (EXP) or control (CTR). Randomization will be achieved by computer-generated permuted block of 4 with stratification according to sex. Research staff and participants will be blinded to group allocations.

**Intervention.** Participants will be screened and baseline measures will be performed within their first 3 visits to the GDH. Upon randomization, EXP group will ingest a supplement of flavored whey protein isolate with added pure leucine (3 g) twice daily, before breakfast and before bedtime. Doses are adjusted per body weight as follows: 20 g, 25 g or 30 g per category of <65 kg, 65-75 kg and >75 kg of body weight respectively (see Appendix Table 2 for nutritional details). Supplements will be offered during 8 weeks (average time of GDH program attendance) and for the following 8 weeks, at home or residence, for a total of 16 weeks. The CTR group will ingest an isocaloric placebo consisting of 30 g maltodextrin (a simple carbohydrate, providing 116 kcal), following the same schedule. Both products will be provided in pre-weighted doses in sterile containers; participants will be instructed to dilute and mix with 125 mL (1/2 cup) water to ingest. The fish oil + vitamin D supplement will be provided as a liquid oil (NutraSea Liquid® from Ascenta). Participants will receive a dosing cup, pre-marked to measure 7.5 mL, providing 1500 IU vitamin D3 + 1125 mg EPA + 750 mg DHA, to be ingested once daily. CTR participants will receive an isocaloric placebo oil (corn oil) to be ingested similarly. Oil supplements may be mixed with the protein or maltodextrin powders or ingested separately according to taste. Participants already taking vitamin D (at lower doses than indicated in exclusion criteria) or omega-3 FA supplements may take part in the study but will be asked to interrupt their supplements for the duration of the study. Compliance will be evaluated by twice-weekly monitoring during GDH visits and frequent phone calls during the

second half of study, by self-reporting in a logbook and return of all empty containers and extra oil; ingestion of 80% of provided doses will be required to remain in the study.

**Outcomes: all outcomes (except body composition) will be measured at baseline (prior to intervention), 8 weeks (last program visit) and 16 weeks (returning visit).**

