### **ETHICAL CONSIDERATIONS**

All participants will provide written informed consent. Participants of both arms will benefit from a full nutritional counseling by the PI or the graduate student involved in this study, to optimize their nutritional intake in addition to the standard of care of the GDH program. Those randomized to the EXP group might further benefit from the supplement, in improving muscle mass strength and physical function, according to our hypothesis.

***Intervention products and doses:*** The whey protein isolate, leucine and maltodextrin (placebo) powders are commercially available for human use and safe to ingest at the proposed doses. All will be purchased from ProteinCo Canada, Cowansville, QC, which certifies a Pharmaceutical Grade Purity. These powders are fairly easy to dissolve in water with some mixing and have a sweet taste. The total amount of protein supplemented per day (36 g, 45 g or 54 g) will increase total daily protein intake to 1.2-1.5 g/kg/day, depending on current intake. This range is recommended by at least two international expert groups and recognized as safe for the older population. This dose is however not recommended for persons with severe kidney diseases; therefore, those having such diagnosis or an estimated glomerular filtration rate (eGFR) below 30 mL/min/SA will not be eligible to participate. The free leucine (3 g) added to the whey protein will total 6 g, twice per day = 12 g, which is below the tolerable upper intake level (UL) and safe limit in humans of >550 mg/kg/d, equivalent to 30-39 g/d depending on

weight. The leucine purity, of 99%, has been confirmed by LC-MS/MS and will be assessed for new lots purchased.

Vitamin D: the daily doses of  $\geq 1966.7$  IU (1966.7 IU, 1983.3 IU or 2100 IU depending on the body weight) of vitamin D3 is desirable to augment and reach serum 25(OH)D of  $\geq 80$  nmol/L, based on several studies mostly on osteoporosis and fractures; it is well below the tolerable upper intake level of 4000 IU/day (DRIs) for adults >70 years.

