## Appendix

**Table 1. Information on Dietary Supplements to be used**

| Supplement and ingredients                                                                                | Brand Name/Company                                             | Health Canada NPN | Daily Dose ingested                                                                                                   | UL                                    |
|-----------------------------------------------------------------------------------------------------------|----------------------------------------------------------------|-------------------|-----------------------------------------------------------------------------------------------------------------------|---------------------------------------|
| Experimental supplement                                                                     |                                                                |                   |                                                                                                                       |                                       |
| Whey protein isolate (vanilla flavored)

- Protein (27g/30g dose)
- Vitamin D3 (100 IU/30g dose) | New Zealand Whey Protein Isolate/ The Protein Company ATW Inc. | 80054732          | 2 x 20 g = 40 g
2 x 25 g = 50 g
2 x 30 g = 60 g

36 g
45 g
54 g

66.7 IU
83.3 IU
200 IU | N/A

4000 IU/d                  |
| Leucine                                                                                                   | ProteinCo Leucine Powder/ The Protein Company ATW Inc.         | 80062837          | 2 x 3 g = 6 g                                                                                                         | 550 mg/kg/d                           |
| Fish oil containing vitamin D (flavored) :
- EPA
- DHA
- Vitamin D3                              | NutraSea +D/ Ascenta                                           | 80050462          | 7.5 mL oil =

1125 mg
750 mg
1500 IU                                                                      | EPA + DHA :
5 g/d

4000 IU/d |

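### The instructions on participants' own vitamin D are inconsistent, and the stated daily totals hold only if everyone also takes 400 IU/d of their own

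*Protocol*

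**What the plan says.** Four places in the protocol bear on this.

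- **METHODS, Participants.** Users of vitamin D at 800 IU/d or more are admitted and "will be asked to reduce their dose to 400 IU/d". Where vitamin D was prescribed, "the subjects' physician will be informed to change the current prescription to 400 IU/d for the study duration". The exclusion list in the same paragraph contains no vitamin D dose.
- **METHODS, Intervention.** "Participants already taking vitamin D (at lower doses than indicated in exclusion criteria) or omega-3 FA supplements may take part in the study", but these participants "will be asked to interrupt their supplements for the duration of the study". The study oil is described as "providing 1500 IU vitamin D3 + 1125 mg EPA + 750 mg DHA, to be ingested once daily".
- **ETHICAL CONSIDERATIONS, vitamin D paragraph.** The daily vitamin D3 intake is given as at least 1966.7 IU, and by weight category as "1966.7 IU, 1983.3 IU or 2100 IU depending on the body weight". It is justified by a serum 25(OH)D target of at least 80 nmol/L and compared with an upper level of 4000 IU/day.
- **Appendix Table 1.** The whey powder is listed with "Vitamin D3 (100 IU/30g dose"), and the daily vitamin D from whey in the three weight categories as "66.7 IU 83.3 IU 200 IU".

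**The concern.** The two METHODS paragraphs do not describe the same rule. One reduces higher-dose users to 400 IU/d and gives no clear instruction for users below 800 IU/d, because the sentence on prescriptions can be read as covering any prescription or only those of 800 IU/d or more. The other stops vitamin D in users below an exclusion dose that does not exist, and its wording implies that users above that dose are excluded, although the first paragraph admits them. For omega-3 the two paragraphs agree: own supplements stop. Only for vitamin D do they diverge.

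The ethics section appears to rest on a third position, in which everyone takes 400 IU/d of their own. Vitamin D is one of the tested components. Background intake beneath the study dose, in both arms, would therefore depend on prior use and on which paragraph staff follow, and the intake stated in the ethics section would be wrong for part of the experimental arm.

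**Working it through.** **Inputs**

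- Study oil: 1500 IU/d (METHODS, Intervention; Appendix Table 1).
- Whey vitamin D per day as printed: 66.7, 83.3 and 200 IU (Appendix Table 1).
- Whey content: 100 IU per 30 g (Appendix Table 1).
- Whey doses: 20, 25 or 30 g twice daily (METHODS, Intervention).
- Stated totals: 1966.7, 1983.3 and 2100 IU (ETHICAL CONSIDERATIONS).

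**Step 1. Reproduce the stated totals.** Implied own vitamin D = stated total − oil − printed whey.

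- Under 65 kg: 1966.7 − 1500 − 66.7 = 400 IU
- 65 to 75 kg: 1983.3 − 1500 − 83.3 = 400 IU
- Over 75 kg: 2100 − 1500 − 200 = 400 IU

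The totals reproduce exactly, but only with 400 IU/d of own vitamin D in every category. No condition is attached.

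**Step 2. Study products alone, printed figures.**

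- 1500 + 66.7 = 1566.7 IU
- 1500 + 83.3 = 1583.3 IU
- 1500 + 200 = 1700 IU

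All three are below the stated minimum of 1966.7 IU, by 400, 383.4 and 266.7 IU.

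**Step 3. Check the whey figures.** Daily whey vitamin D = 2 × dose × 100/30.

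- 20 g: 2 × 20 × 100/30 = 133.3 IU (one dose: 66.7)
- 25 g: 2 × 25 × 100/30 = 166.7 IU (one dose: 83.3)
- 30 g: 2 × 30 × 100/30 = 200 IU (one dose: 100)

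The first two printed values are for one dose and the third is for two, although the column is headed as a daily dose.

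**Step 4. Totals with two whey doses in every category.**

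| Weight | Stated | Own vitamin D 0 | Own vitamin D 400 IU/d |
|---|---|---|---|
| <65 kg | 1966.7 | 1633.3 | 2033.3 |
| 65-75 kg | 1983.3 | 1666.7 | 2066.7 |
| >75 kg | 2100 | 1700 | 2100 |

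With the whey corrected, a participant taking no own vitamin D still misses the 1966.7 IU minimum, by 333.4, 300.0 and 266.7 IU. Every value in the table is below 4000 IU/d.

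**Step 5. The METHODS rules side by side.**

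| Prior use | Participants paragraph | Intervention paragraph |
|---|---|---|
| 800 IU/d or more | reduce to 400 IU/d | implied excluded |
| below 800 IU/d | no clear instruction | interrupt, if the missing exclusion dose is taken to be 800 IU/d |
| none | no instruction needed | no instruction needed |

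If the missing dose is read as 800 IU/d, someone arriving on 1000 IU/d keeps 400 IU/d and someone arriving on 600 IU/d goes to zero. That difference of 400 IU/d is 400/1500 = 27% of the vitamin D in the study oil. If staff follow the Participants paragraph alone, a user below 800 IU/d could continue unchanged, and the spread would be wider.

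**The case against.** The strongest reply is that the two METHODS rules cover different dose bands. If the reference to exclusion criteria is a mislabelled pointer to the 800 IU/d threshold, higher-dose users reduce, lower-dose users stop, and no one participant receives two conflicting instructions. This stands in part: the rules need not collide for one person. It does not rescue the text. The reader has to supply a threshold the exclusion list does not contain, the wording still implies that higher-dose users are excluded, and the ethics totals still add 400 IU for people who would be stopped or who never took any.

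A reader might go further and infer that the vitamin D contrast between arms is undefined or biased. The documents do not support that. Neither rule differs by arm, prior use is fixed before randomisation, and allocation is blinded. Under either rule the assigned difference is oil plus whey against placebos for which no vitamin D is listed. Chance imbalance in prior use is possible with 40 participants stratified only by sex, but that is chance and not bias.

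It is also fair to say that the pilot is declared not powered for differences in the main outcomes, that 25(OH)D is listed among the other measures, and that 80 nmol/L is a dosing rationale and not an endpoint. These points limit the consequence. They do not make the instruction or the totals correct.

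**Conclusion.** The inconsistency stands. No reading makes the two METHODS paragraphs and the ethics totals all true. The totals carry an unstated 400 IU/d of own vitamin D in every weight category, and two of the three also understate whey vitamin D, by 66.7 IU (133.3 − 66.7) and 83.4 IU (166.7 − 83.3).

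The consequence is limited to three things: heterogeneous background intake in both arms, a 25(OH)D response that is harder to interpret, and a stated intake in the ethics section that some participants will not reach. Sample size and the feasibility criteria are unaffected. A safety problem should not be inferred either, since every total recomputed here, from 1566.7 to 2100 IU/d, is well below the protocol's own 4000 IU/d limit.

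The result rests on Table 1's content of 100 IU per 30 g and on two whey doses a day. The protocol does not say how many participants take vitamin D or at what dose, so the number affected is unknown.

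**What to change.** Reconcile the Participants and Intervention paragraphs of METHODS, the vitamin D paragraph of ETHICAL CONSIDERATIONS and Appendix Table 1:

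1. State the instruction on own vitamin D consistently for every level of prior use, including prescribed vitamin D. Whether the rule is uniform or banded by dose, and what it is, is for the investigators.
2. Remove the reference to a vitamin D dose in the exclusion criteria, or supply that dose.
3. Put the Table 1 whey figures on the same daily basis in all three weight categories.
4. Recompute the ethics totals, showing vitamin D from study products separately from any own vitamin D, and restate the minimum to match.

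The cost is protocol wording and a short recalculation. Design, sample size and outcomes do not change.

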### **STATISTICAL ANALYSIS**

This is a pilot study designed to generate data on feasibility, acceptance and compliance to the supplement and study tests; it is not powered for identifying statistical differences in the main outcomes. The sample size required for the full study will be of approximately 160 participants (80 EXP, 80 CTR). This calculation is based on an expected difference of 1 second in reducing the chair-stand time between the 2 groups, acknowledging that the CTR will also gain from the rehab program, and from standard deviation from published studies. This sample size should be enough to detect differences in handgrip and leg strength and in appendicular muscle mass accretion. Pilot data will therefore be crucial to confirm these calculations. We aim to recruit 40 participants to provide confidence intervals to determine the final RCT sample size.

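### A single fixed block of 4 within sex lets up to a third of allocations be foreseen if the products reveal earlier ones; varying, undisclosed block sizes remove most of that certainty

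*Protocol*

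**What the plan says.** The Study design paragraph under METHODS fixes the method: "Randomization will be achieved by computer-generated permuted block of 4 with stratification according to sex". It adds that "Research staff and participants will be blinded to group allocations". It mentions no variation in block size, and does not say who holds the list or whether recruiting staff know the block size. The pilot size is under STATISTICAL ANALYSIS: "We aim to recruit 40 participants to provide confidence intervals".

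The products are described in the Intervention paragraph and Appendix Table 1.

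- Experimental powder: "flavored whey protein isolate with added pure leucine (3 g) twice daily", with whey doses of "20 g, 25 g or 30 g per category of <65 kg, 65-75 kg and >75 kg of body weight respectively".
- Control powder: "The CTR group will ingest an isocaloric placebo consisting of 30 g maltodextrin", with no weight categories. The appendix also gives one placebo dose, 2 x 30 g daily.
- Oils: the control oil is corn oil. Under ETHICAL CONSIDERATIONS the protocol lists a fishy aftertaste and burping as typical of fish oil, and chooses a fruit-flavoured product to limit them. No flavouring or taste matching is described for the corn oil.
- Handling: doses come pre-weighed, participants mix them, and empty containers and leftover oil are returned. Compliance is checked twice a week during the day-hospital phase, then by phone.

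**The concern.** In a balanced block of known size, the remaining allocations are fixed once one arm is used up. With a single size of 4 this happens often. It does no harm if nobody can tell what earlier participants received, so the design leans on blinding. The product descriptions leave that blinding less secure than the protocol states, because dose mass differs by arm and the oils may differ in taste.

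At stake is allocation concealment. Someone who could foresee the next assignment might, even unintentionally, influence who is enrolled or in what order. Some eligibility criteria require judgement (recovery from stroke, stabilised weight loss, severity of neurologic disease), and baseline measures may fall anywhere within the first three visits. Selection of this kind cannot be dependably removed in the analysis. Physical performance and strength are listed among the primary outcomes, and the pilot data are meant to confirm the full trial's sample size.

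**Working it through.** The protocol gives no predictability figure to reproduce, so the check starts from the design.

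**Inputs.** Block size 4, two sex strata, two arms (Study design); 40 participants (STATISTICAL ANALYSIS). The 1:1 ratio is an assumption for the pilot, taken from the 80 and 80 planned for the full trial. The sex split is not given, so every split of 40 was examined.

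**Certainty in a block of 4.** There are 6 equally likely orders of two experimental and two control assignments. An assignment is certain when the earlier ones in the block have used up one arm.

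- Positions 1 and 2: probability 0.
- Position 3: certain if the first two match, 2 of 6 orders = 1/3.
- Position 4: always certain, 1.

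Expected certain assignments = 0 + 0 + 1/3 + 1 = 4/3 per block, and (4/3)/4 = 33.3%.

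**Best guess in a block of 4.** The chance of a correct guess by position is 1/2, 2/3, 2/3 (= 1/3 x 1 + 2/3 x 1/2) and 1. The sum is 17/6, and (17/6)/4 = 17/24 = 70.8%, against 50% under simple randomisation.

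**Forty participants in two strata.** If both strata fill complete blocks (for example 20 and 20), 10 x 4/3 = 13.3 assignments are certain, 33.3%. If each stratum ends two into a block (for example 18 and 22), 9 x 4/3 = 12.0 are certain, 30.0%. Remainders of one and three give 9 x 4/3 + 1/3 = 12.3, 30.8%. The range is 30.0% to 33.3%.

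**Can earlier allocations be known?** The appendix gives 27 g protein per 30 g whey, a fraction of 0.9. The daily protein of 36, 45 and 54 g equals 0.9 x 40, 50 and 60 g, so the 20, 25 and 30 g doses are whey alone and the 3 g leucine is additional.

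| Body weight | Experimental, whey alone | Experimental, with leucine | Control | Gap with leucine |
|---|---|---|---|---|
| <65 kg | 20 g | 23 g | 30 g | 7 g |
| 65-75 kg | 25 g | 28 g | 30 g | 2 g |
| >75 kg | 30 g | 33 g | 30 g | 3 g |

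If leucine is packed with the whey, the arms differ in all three categories, but clearly only below 65 kg. On whey alone they differ in two of three.

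**Alternatives, all earlier allocations known.** Fixed sizes were enumerated exactly. Varying sizes were simulated (4,000 sequences of 20 per stratum) with an observer who knows which sizes are in use, but not which applies, and updates after each assignment.

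| Scheme | Certain in advance | Correct best guess |
|---|---|---|
| Fixed 4 | 33.3% | 70.8% |
| Fixed 6 | 25.0% | 68.3% |
| Fixed 8 | 20.0% | 66.6% |
| Random 4/6 | 5.8% | 68.5% |
| Random 4/6/8 | 2.4% | 67.1% |

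Varying the size removes most of the certainty and little of the guessability.

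**Imbalance.** An incomplete block of 4 can leave the arms 2 apart in a stratum, and an incomplete block of 6 can leave them 3 apart. Over two strata the extremes are 4 and 6 of 40.

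**The case against.** The strongest reply is that nothing here is an error. Computer-generated blocks of 4 stratified by sex are an ordinary choice for 40 participants, stating the block size is good reporting, and custody of the list is often set out elsewhere. The trial is a pilot, expressly not powered for differences in the main outcomes. The protocol also says that all eligible patients will be invited, which limits discretion over whom to approach. All of this stands, and it is why the point is an inexpensive improvement and not a fault that invalidates the design.

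Three stronger readings are tempting but unsupported.

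- A reader might infer that the blinding is certain to fail. The protocol gives doses, not container size or opacity. Containers are returned empty, so the returned pack carries no powder-mass cue. Differences of 2 or 3 g may pass unnoticed.
- A reader might infer that taste cannot be masked. The active oil is flavoured to limit the aftertaste, and the protocol does not say whether the corn oil is flavoured. Any taste cue reaches participants first and staff only through what participants report.
- A reader might infer that one small team handles both products and recruitment. The coordinator approaches patients, but no role is named for the compliance checks, and other tasks go to other staff.

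It is also fair to object that product masking is the larger issue and that varying the blocks barely changes guessing. Both are correct. What the change does remove is nearly all of the assignments that could be foreseen with certainty.

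**Conclusion.** The point holds as a modest one. A single stated block size of 4 within sex relies on earlier allocations staying hidden, and the stated differences in powder mass and oil make partial unmasking plausible. The worst case is 33% of assignments certain in advance (12.0 to 13.3 of 40, or 30% to 33%) and 71% guessable.

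These figures assume 1:1 blocks and an observer who knows the block size and every earlier allocation in the current block before the next enrolment. They are a ceiling: cues arise only after product is dispensed or used, and their strength depends on body weight. The documents give no basis for a realistic rate, and they do not show that selection would occur.

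**What to change.** Replace the single block size by sizes that vary at random within each sex stratum, for example 4 and 6. Have the list generated and held by someone who takes no part in recruitment, and keep the sizes out of any text that recruiting staff see. The protocol need only say that the sizes vary and are recorded in a restricted document. Worst-case certainty falls from 33% to about 6%; correct guesses fall only from 71% to about 69%.

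The cost is a regenerated list, which assumes enrolment has not begun, and a possible imbalance of up to three per sex stratum instead of two.

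Separately, the sponsor should reconcile the blinding statement with the differences in mass and flavour between the products. Varying the block size complements that work and does not replace it. No dose is proposed here.
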